#### Socially evaluated cold-pressor test

2.4.4.

The socially evaluated cold-pressor test (SECPT) is a validated stress paradigm that induces robust increases in subjective stress ratings, blood pressure, and salivary cortisol levels (Schwabe et al., 2008; Schwabe & Schächinger, 2018). The SECPT protocol was adapted after consultation with our advice committee of experts – people with personal experience of PTSD – not to include a camera set-up, as this was considered too stressful for certain (social anxiety) subpopulations. For details about its implementation in the current study, see the Supplementary Material (S8).

#### Fear conditioning and extinction task

2.4.5.

To assess the strength and generalization of safety learning within an experimental setting, the current study employs a 2 day differential fear acquisition, extinction, and extinction recall task in a virtual environment (VE) with contexts as occasion setters (Figure 2). This task was adapted from previous studies and subsequently validated in a study with healthy young adults (de Nooij et al., 2021; de Voogd et al., 2020; Wirz et al., 2021). The task consists of two different VEs (natural scene and city scene) to allow repeated measurements within the crossover design of this study. Contexts for experiences are defined by three different houses within each VE. The conditioned stimuli (CSs) are simple geometric shapes and the unconditioned stimulus (US) is an electric shock to the fingers. The task consists of three phases: (1) fear acquisition, (2) fear extinction, and (3) recall. In each phase, the participant navigates within the three-dimensional VE using a joystick. After navigating to one of the houses, the participant is presented with a trial block of a two-dimensional task. During each trial, the participant provides a shock expectancy rating (SER) on a scale from 1 (‘certainly no shock’) to 5 (‘certainly a shock’). Primary outcomes consist of fear-related measures of autonomic nervous system response, particularly the skin conductance response (SCR) and pupil dilation response (PDR); these are assessed during each phase of the task. Further details on the task, experimental set-up, and counterbalancing are outlined in the Supplementary Material (S9).

**Figure 2. F0002:**
[figure not shown]
Fear conditioning and extinction task. (a) The task consists of a fear acquisition, fear extinction, and extinction recall task. In this study, hydrocortisone or placebo is administered 45–55 minutes prior to the fear extinction task. This fear extinction task is completed during functional magnetic resonance imaging (fMRI) scanning. Outcome measures are psychophysiological measurements (pupil, skin conductance) and shock expectancy ratings during all tasks, and neuroimaging during the fear extinction task. (b) To accommodate the crossover design of this study, the task has two virtual environments (nature and city environment) with three houses each. These houses function as occasion setters, i.e., ‘contexts’ for the experiences (acquisition, extinction, novel). (c) Task procedures to start a task block. The participant is first instructed to enter a booth. Inside this booth, they are presented with the house to which they should navigate. They should also rate on a five-point scale whether they expect to receive at least one shock within that house in the upcoming block. Entering a booth within the correct house triggers the start of a block. (d) Task procedures within a block, per trial. The participant is presented with a fixation cross before presentation of a conditioned stimulus (CS). During CS presentation, they should rate on a five-point scale whether they expect to receive a shock based on the stimulus that is being presented. At the end of stimulus presentation, depending on the task and trial, negative reinforcement with an electric shock to the fingers may follow. (e) Two sets of three shapes that function as CSs within the paradigm.

##### Task phases

2.4.5.1.

*Fear acquisition.* Three different CSs are presented in four blocks. Each block consists of four trials per CS, totalling to 12 trials per block. One CS is never followed by shock (CS−), whereas two other CSs (CS+s) are sometimes followed by shock according to a 50% reinforcement schedule. All blocks are completed within the same house; this house is established as the ‘acquisition context’.*Fear extinction.* The CS− and one of the two CS+s are presented in four blocks. Each block consists of four trials per CS, totalling to eight trials per block. Here, the included CS+ is being extinguished (CS+E) as no shocks are administered during this phase. The CS+ that is omitted from this phase remains unextinguished (CS+U). All blocks are completed within the same house, differently from the fear acquisition phase; this house is established as the ‘extinction context’.*Extinction recall.* All three CSs (CS+E, CS+U, and CS−) are presented in six blocks. Each block consists of two trials per CS, totalling to six trials per block. The first two blocks are presented within the ‘extinction context' house, the next two blocks within the ‘novel context' house, and the last two blocks within the ‘acquisition context' house.

##### Practice tasks

2.4.5.2.

In relation to the fear conditioning and extinction task, two practice tasks were developed: one to practise navigation with the joystick and for familiarization with the VE, and one to practise giving scores with the joystick and more generally to practise the required course of actions (for details, see Supplementary Material S9).

#### Neuroimaging

2.4.6.

Details of magnetic resonance imaging (MRI) data acquisition are described in the Supplementary Material (S10).

##### Task-based fMRI: fear extinction

2.4.6.1.

Neural responses associated with extinction learning are assessed during the fear extinction task, as previously described.

##### Task-based fMRI: emotion processing

2.4.6.2.

Neural responses during implicit emotion processing are assessed using an adaptation of an emotional face matching task (Hariri et al., 2002). The current task version was implemented by the DynaMORE consortium (for details, see Wackerhagen et al., 2023). In short, grey-scale faces with angry and fearful expressions that should be matched are presented during the emotion condition, whereas in the shape condition, geometric shapes (circles, horizontal ellipses, and vertical ellipses) that should be matched are presented. The task consists of eight blocks of six trials that alternate between conditions.

##### Resting-state fMRI

2.4.6.3.

For resting-state scans, participants are presented with a fixation cross (white cross on black background). They are instructed to keep their eyes open and have their thoughts flow freely, but refrain from repetitive mental activities such as counting.

### Procedure

2.5.

Additional information on study procedures can be found in the Supplementary Material (S11).

#### Recruitment

2.5.1.

Participants from the PTSD group are recruited via Pro Persona and Kairos, which are collaborating mental healthcare institutions located in and around Nijmegen. In addition, following approval of a study amendment, participants from the PTSD group are also recruited from the general population via (social media) advertisements, distribution of posters and flyers, and personal and professional networks. PTSD group participants are directed to a study website with short informational videoclips and other information. They are personally contacted and complete a telephone screening to assess inclusion and exclusion criteria. Participants from the control group are recruited from the general population via (social media) advertisements and distribution of posters and flyers, and receive information and register via a study website for the control group.

#### Participant inclusion

2.5.2.

All participants provide informed consent at their first visit. This is followed by verification and registration of inclusion and exclusion criteria, and collection of general information.

#### Screening visit

2.5.3.

##### Screening visit for PTSD group

2.5.3.1.

The screening visit only applies to PTSD patients who were recruited from the general population. Based on the preference of the participant and feasibility, this visit can be scheduled on location or as an online visit. During this visit, an online questionnaire and CAPS-5 clinical interview are administered to the participant. The participant is immediately informed about inclusion or exclusion in this study, depending on whether they meet classification criteria for PTSD or not.

##### Screening visit for control group

2.5.3.2.

The participant completes the MACE as an online questionnaire, followed by a MINI assessment. Based on their results, the participant is immediately informed about inclusion in or exclusion from this study (for details, see Supplementary Material S1).

#### Observational study (Part A)

2.5.4.

##### First visit (A1)

2.5.4.1.

During this visit, the participant completes MACE (if not previously completed) and several other online questionnaires/assessments. Subsequently, they receive materials and in-person instructions for the DST procedure (for details, see Supplementary Material S7).

##### Second visit (A2)

2.5.4.2.

This visit is scheduled in in the afternoon [SECPT from 1 p.m. (13:00 h)] to avoid any influence of higher morning cortisol levels. The researcher receives the materials for the DST procedure from the participant and evaluates the procedure. Then, the participant completes the PCL-5 and several other online questionnaires before participating in the SECPT procedure. Here, saliva samples are collected at 15, 30, 45, 60, 75, and 90 minutes after the onset of the stress procedure. Lastly, venous blood is sampled by a trained research nurse at the Radboud University Medical Center.

#### Pharmacological intervention and fMRI study (Part B)

2.5.5.

Owing to the crossover design, this study part consists of two sessions that are scheduled with a 4–6 week interval. The sessions are identical, except for the type of drug administered (hydrocortisone or placebo) and the version of the fear conditioning and extinction task (different VE with different set of CSs). Each session includes two visits to the Donders Centre for Cognitive Neuroimaging on subsequent days (Figure 3). Before each visit, participants receive instructions for quality assurance of data (for details, see Supplementary Material S6).

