### Pharmacological intervention

2.3.

In part B of the study, to investigate glucocorticoid effects on extinction learning and brain activity, participants ingest 20 mg hydrocortisone prior to extinction learning in one session, and placebo prior to extinction learning in the other session. The order of medication administration is double-blind and counterbalanced across participants (for details see Supplementary Material S4).

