##### Statistical modelling

2.6.2.2.

1. Investigate whether patients with HPA-axis dysregulation show impairments in extinction learning relative to patients without HPA-axis dysregulation, and whether this is accompanied by different neural responses during extinction learning in brain regions associated with fear expression and extinction.

This objective will be investigated with data from placebo sessions only. At the psychophysiological level, we expect HPA-axis dysregulation to be associated with lower strength of the extinction memory, indicated by lower differential responses for CS+U vs CS+E and/or higher differential responses for CS+E vs CS− during the extinction recall task. This will be modelled with a two-way ANOVA of averaged differential responses during the first block, which is within the extinction context and contains two presentations of each CS. Higher generalization of the extinction memory for the HPA-axis normalized group would be indicated by a context interaction effect that shows less renewal of fear, i.e. a lower increase of differential effects upon stimulus presentations within the novel and acquisition contexts. These comparisons may be affected by an overall attenuation of fear responses due to re-extinction over the course of the extinction recall task. This effect will be investigated with a 2 (group) by 3 (context) mixed ANOVA of averaged differential responses during the first block of each context. Both models will include the covariate order of medication administration, and, if appropriate, the covariates age and gender. Outcome measures SCR, PDR, and SER will be included in separate models, but since these measures of conditioning are complementary, no multiple comparisons correction will be applied. At the level of neuroimaging, differences in extinction learning signalled during the fear extinction task could be underlying the differences at the behavioural level. Here, we would expect different neural responses in brain regions and networks associated with (context-dependent) extinction learning for patients with HPA-axis dysregulation, which could also be associated with less successful recall of the extinction memory.

2. Investigate whether the subgroup of PTSD patients with HPA-axis dysregulation particularly benefits from hydrocortisone administration (versus placebo) to improve the strength and generalization of extinction memories.

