To answer the main objective of the pharmacological intervention study, the aforementioned psychophysiological models will be extended with data from the hydrocortisone sessions (thus adding a within-subjects category for medication). Period effects may follow from the crossover design and will be accounted for by defining a medication-by-order interaction effect. Based on previous research, we hypothesize a group-by-medication interaction effect, indicating greater strength and/or generalization of the extinction memory following administration of hydrocortisone, that is most pronounced for the HPA-axis dysregulation group.

3. Investigate underlying neural mechanisms of glucocorticoid administration (versus placebo) to improve extinction learning.

Recruitment of neural networks associated with (context-dependent) extinction learning for patients with HPA-axis dysregulation (see point 1 above) would be expected to enhance following hydrocortisone administration. Pharmacological effects and their potential interactions with HPA-axis dysregulation are primarily investigated during the extinction learning task, but will also be supported by the following analyses: (1) amygdala (and salience network) reactivity to the emotion processing task, which we expect to be reduced after hydrocortisone administration; and (2) resting-state connectivity in networks associated with (context-dependent) extinction learning – ventromedial prefrontal cortex–amygdala connectivity, in particular – which we expect to be enhanced after hydrocortisone administration.

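### The part B models list no term for task version, which changes between each patient's two sessions; if version is crossed with drug order, precision is lost but validity is not

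*Protocol article*

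**What the plan says.** All references are to the Protocol article.

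- **Sessions (section 2.5.5).** The two sessions are the same apart from the drug and "the version of the fear conditioning and extinction task (different VE with different set of CSs".
- **Versions (section 2.4.5).** "The task consists of two different VEs (natural scene and city scene) to allow repeated measurements within the crossover design of this study". On allocation, the section says only: "Further details on the task, experimental set-up, and counterbalancing are outlined in the Supplementary Material (S9".
- **Drug order (section 2.3).** "The order of medication administration is double-blind and counterbalanced across participants".
- **Objective 1 models, placebo sessions only (section 2.6.2.2).** The factors are group and, for generalization, context. "Both models will include the covariate order of medication administration, and, if appropriate, the covariates age and gender".
- **Objective 2 models (section 2.6.2.2).** "the aforementioned psychophysiological models will be extended with data from the hydrocortisone sessions (thus adding a within-subjects category for medication". On period: "Period effects may follow from the crossover design and will be accounted for by defining a medication-by-order interaction effect". The hypothesis is a group-by-medication interaction.
- **Objective 3 (section 2.6.2.2).** The article names no covariates. MRI analyses are left to S14, and details of the psychophysiological analysis to S13.

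Task version is not among the terms named for any of these models.

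**The concern.** Two session-level features other than drug change within each patient: the period, and the task version with its environment and stimulus set. The plan names a term for the first and none for the second.

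The main part B test, group by medication, rests on each patient's hydrocortisone-minus-placebo difference. If half the patients meet hydrocortisone in the nature version and half in the city version, in both drug orders, a difference between versions adds to that difference in some patients and subtracts from it in others. The medication-by-order term cannot remove this, because version then varies within each order. It stays in the residual and widens the interval for the interaction. In the placebo-only models of objective 1, version varies between patients and adds to the between-patient error in the same way.

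What is at stake is power, in a study of 80 patients split into two subgroups at the median.

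**Working it through.** **Inputs from the article.** Part B has n = 80 (section 2.2). The two groups come from a median split on relative suppression of the cortisol awakening response (section 2.6.2.1), so about 40 each. There are two task versions (section 2.4.5). The model terms are those listed in section 2.6.2.2.

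**Inputs that are assumed.** The article leaves its power calculation to S3, so n = 80 cannot be reproduced here. For illustration: two-sided alpha 0.05, and 80% power for the interaction when versions do not differ. The size of a version effect is not given, so a range is shown.

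**Model.** Let D be the within-patient hydrocortisone-minus-placebo difference, with residual SD 1 after the planned terms. Let v be the mean difference between versions in units of that SD. With version crossed with drug order and equally split, D contains +v for half the patients and −v for the other half. Leaving version out gives

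Var(D) = 1 + v².

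**Calibration.** The interaction detectable with 80% power is (1.960 + 0.842) × √(2/40) = 0.626.

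**Power without a version term.** Power = Φ(2.802/√(1 + v²) − 1.960), and effective n = 80/(1 + v²).

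| v | Variance factor | Effective n | Power |
|---|---|---|---|
| 0 | 1.00 | 80.0 | 80.0% |
| 0.1 | 1.01 | 79.2 | 79.6% |
| 0.2 | 1.04 | 76.9 | 78.4% |
| 0.3 | 1.09 | 73.4 | 76.5% |
| 0.5 | 1.25 | 64.0 | 70.7% |

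**Simulation check.** Each scenario had 6,000 runs, with 40 patients per order, version crossed with order, a period effect present, groups assigned at random, and least squares on D.

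| v | Power, planned terms | Power, version added | Mean interaction, planned terms (true 0.626) | Type I error, planned terms |
|---|---|---|---|---|
| 0 | 78.5% | 78.2% | 0.625 | 0.051 |
| 0.2 | 77.5% | 78.9% | 0.629 | 0.050 |
| 0.5 | 68.4% | 77.7% | 0.620 | 0.049 |

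Simulated power is a little below the formula because it uses the t distribution with estimated variance. The pattern agrees: no bias, nominal type I error, and a power loss that grows with v and disappears once version is in the model.

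**Alternative allocation.** If the same version always comes first, version is the same as period. The medication-by-order term then absorbs it. At v = 0.5 the planned model has simulated power of 78.2%, so nothing is lost.

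**Balance within the subgroups.** The median split does not guarantee equal version shares in the two groups. With 40 of 80 patients in a group, the SD of the version count is √(40 × 0.5 × 0.5 × 40/79) = 2.25. The difference in version share between groups has SD 2 × 2.25/40 = 0.1125, so its 95% chance range is ±1.96 × 0.1125, about 22 percentage points. This is not an additional loss, because the factor 1 + v² already includes it. It shows how the noise reaches the interaction.

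**The case against.** The strongest case against is that a journal article need not list every nuisance term. It sends counterbalancing to S9, psychophysiological analysis to S13 and MRI analysis to S14, and any of these may settle the matter. That stands as a condition on the fix. It does not remove the point, because section 2.6.2.2 does list its model terms, down to order and optional age and gender, and leaves out a session-level factor that the article itself describes.

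Second, crossing of version with drug order is inferred. Section 2.3 counterbalances only the order of medication, and section 2.4.5 does not say what the task counterbalancing covers. This stands, and under a fixed version sequence the point falls away.

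Third, v may be small. The outcomes are differential responses between stimuli, so a version effect common to all stimuli cancels before modelling. The two environments were also built for repeated use, in a task validated in healthy young adults. This stands too: at v of 0.2 or less the loss is under 2 points. The article does not, however, state that the versions are equivalent in differential responding.

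A reader might go further and infer that drug and version are confounded, or that the interaction test is invalid. The documents do not support that. Nothing says that one version always accompanies hydrocortisone, and with version balanced across drug order the estimate is unbiased and type I error is nominal. A reader might also extend the point to all of objective 3. The face-matching and resting-state scans are not described as having an environment version, so it does not apply to them.

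**Conclusion.** The point holds as a free improvement in precision. The listed part B models have no term for task version. If version is crossed with drug order, its effect on differential responding stays in the within-patient error of the group-by-medication test. With 80% power assumed at v = 0, the loss runs from 0.4 points at v = 0.1 to 9.3 points at v = 0.5.

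This rests on three things that the article does not settle: that version is crossed with order, that v is not negligible, and that S9, S13 and S14 do not already provide the term. The size of the effect in the placebo-only models was not calculated.

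**What to change.** First state how version is allocated relative to session and drug order. If it is tied to session, or if S9, S13 or S14 already model it, saying so is enough. Otherwise:

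- add task version (nature/city) as a within-patient fixed factor in the objective 2 crossover models;
- do the same for the drug contrast in the extinction-task fMRI of objective 3, but not for the face-matching or resting-state scans;
- add it as a between-patient covariate in the placebo-only models of objective 1.

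The cost is one degree of freedom and no new data, since the assigned version is known by design. If the versions turn out equivalent, the price is at most about one point of power (78.5% against 78.2% in the simulation at v = 0). The term should be fixed before unblinding, so that including it is not a choice made after seeing results.

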**Figure 3. F0003:**
[figure not shown]
Timeline of study procedures per session in the pharmacological intervention and functional magnetic resonance imaging (fMRI) study. The first study visit typically starts around 10 or 11 a.m. (10:00 or 11:00 h), and the next-day visit typically starts around 3.15 or 4.15 p.m. (15:15 or 16:15 h).

